**Safety Measures**																					
	C-SSRS^g^ (past 6 months)			✓																	
	C-SSRS (since last visit)					✓			✓		✓		✓		✓		✓		✓		
	BDI^h^					✓			✓		✓		✓		✓		✓				
	SAFTEE^i^										✓		✓		✓		✓				

^a^CHQ: Cambridge Hopkins Questionnaire.

^b^sIRLS: self-administered International Restless Legs Syndrome Severity Rating Scale.

^c^FIQR: Fibromyalgia Impact Questionnaire—Revised.

^d^BPI: Brief Pain Inventory.

^e^PHQ-9: Patient Health Questionnaire—9.

^f^PROMIS: Patient-Reported Outcomes Measurement Information System.

^g^C-SSRS: Columbia Suicide Severity Rating Scale.

^h^BDI: Beck Depression Inventory.

^i^SAFTEE: systematic assessment for treatment emergent events.

Eligible participants will be enrolled in the study at visit 2, during which questionnaires to characterize the sample will be completed (Table 1). Before visit 2, participants will be randomized to the morning light treatment, sleep stabilization treatment, or TAU group, and will be mailed the appropriate study supplies (see below for more details). All participants will receive a Fitbit Charge 5 or 6 to wear on their nondominant wrist to track their sleep and activity throughout the 5-week study protocol, along with daily logs to report their subjective experience of sleep and caffeine, alcohol, and medication use. A week later, at visit 3, pre-treatment outcome assessments will be administered, and treatment expectations will be assessed. The randomly assigned treatment condition will then begin the morning after visit 3. Thereafter, there will be weekly visits (visits 4, 5, and 6) to review each participant’s adherence to instructions (sleep timing alone or paired with the use of the Re-timer, depending on treatment group) and to systematically assess side effects (all groups). At visit 7, posttreatment outcome measures will be administered, and study satisfaction will be assessed. Participants will be required to abstain from alcohol and cannabis use within 24 hours of visits, with reminders the day before each visit.

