### Randomization and Blinding

Participants will be randomized to either 4 weeks of morning light treatment (1 hour per day), 4 weeks of sleep timing stabilization alone, or 4 weeks of TAU in a 1:1:1 ratio. Randomization will use a minimization approach to reduce imbalances in important variables, including FIQR score (31-65 vs 66-100 to reflect the divide between mild to moderate symptoms vs severe symptoms), age (18-44 vs ≥45 years to reflect that more circadian disruption is observed in younger participants and the prevalence of FM is higher ≥45 years), biological sex (male or female), and SDOH risk index (0-2 vs 3-6, explained below). Study research assistants assessing outcomes at study visits 3 and 7 will be blinded to treatment assignment and instructed not to discuss any aspect of the treatment with participants. The participants will also be instructed not to discuss the study treatment with the blinded research staff. Otherwise, unblinded study staff will meet with participants weekly to download data from the wrist monitor and Re-timer device (in the morning light treatment group), provide feedback on adherence, and assess treatment side effects.

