### Self-Reported Outcomes

The primary outcome measure is the FIQR [48]. The FIQR consists of 21 items that assess function, overall impact, and symptoms. Total scores range from 0 to 100, with higher scores representing worse functional status. The secondary outcome measure is the Brief Pain Inventory (BPI), which assesses for the presence of pain, pain intensity, and functional interference from pain [53]. The BPI consists of 2 scores (pain severity and pain interference) with higher scores indicating more pain or greater pain interference. The BPI has been validated for fibromyalgia specifically [54,55].

Three additional outcome measures will be explored as potential mediators. The Patient Health Questionnaire-9 (PHQ-9) is a reliable measure of the severity of depressive symptoms [56]. The PHQ-9 consists of 9 items, and higher scores reflect higher levels of depressive symptoms. The Patient-Reported Outcomes Measurement Information System (PROMIS) Sleep Disturbance Short-Form 8b is a reliable measure of sleep quality [57]. Higher scores on the PROMIS Sleep Disturbance Short-Form 8b reflect worse sleep quality. The Morningness-Eveningness Questionnaire (MEQ) [58] will be used as a proxy marker of circadian timing. The MEQ score correlates well with the gold standard circadian phase marker, the dim light melatonin onset [59], and significantly increases towards more “morningness” after 13-28 days of a morning light treatment [60]. This will allow us to confirm an expected phase advance or earlier shift in circadian timing in response to morning light treatment.

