We will conduct an intention-to-treat analysis. We will report descriptive statistics of the data and visually explore the summary statistics by group at each visit. We will analyze both primary and secondary outcomes using a mixed-effects longitudinal data model with participants as random intercepts to account for between-participant variability. Predictors will include post-randomization time, two intervention group indicators with TAU as the referent group, and the interactions of time by group indicators. We will examine the extent and pattern of key missing outcomes data, and if missingness is greater than 15%, we will use logistic regression to assess baseline characteristics predictive of missingness postrandomization and will include those baseline characteristics as covariates in the final model. While FIQR scores will be examined as a continuous variable, we will also examine the proportion of participants who show clinical response (a binary outcome of clinically meaningful improvement (≥30% from baseline) or achieving a treatment response (≥16.8 decrease in FIQR [83]) and analyze the binary outcome variable using a generalized linear mixed model with logit link. We will also explore the severity of restless leg syndrome, obstructive sleep apnea, dispositional trait, and biological sex as potential moderators of any treatment effects.

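### The stated primary model does not plan to adjust for visit 3 FIQR or the minimization factors, which gives up precision the trial could have at no cost

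*Protocol article*

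**What the plan says.** All references are to the protocol article.

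- **Model (Statistical Power and Analysis).** Primary and secondary outcomes are analysed with a "mixed-effects longitudinal data model with participants as random intercepts to account for between-participant variability". The fixed effects are given as: "Predictors will include post-randomization time, two intervention group indicators with TAU as the referent group, and the interactions of time by group indicators".
- **Covariates (same section).** The one stated route is conditional: "if missingness is greater than 15%, we will use logistic regression to assess baseline characteristics predictive of missingness postrandomization", after which the authors "will include those baseline characteristics as covariates in the final model".
- **Allocation (Randomization and Blinding).** "Randomization will use a minimization approach to reduce imbalances in important variables, including FIQR score". FIQR is split at 31-65 versus 66-100. The other factors are age (18-44 versus 45 and over), sex, and SDOH risk index (0-2 versus 3-6).
- **Timing (Procedures and Assessments, text after Table 1).** "Before visit 2, participants will be randomized to the morning light treatment, sleep stabilization treatment, or TAU group". The pretreatment FIQR is collected a week after visit 2, at visit 3. Table 1 also shows a FIQR at the screening phone interview.
- **Power (Statistical Power and Analysis).** 80% for a one-way ANOVA on standardized changes of 0.47, 0.16 and 0.05, with 103 completers per arm and 20% attrition.

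**The concern.** In a trial with a continuous outcome measured before and after treatment, the baseline value is usually the strongest predictor of the final value. An analysis that does not condition on it has wider confidence intervals than the same data allow. The stated predictors leave it out, and they leave out the variables judged important enough to control the allocation.

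The conditional rule does not repair this. It selects covariates from the trial data because they predict dropout, not because they are prognostic or part of the design. A minimization factor may enter this way, but only incidentally.

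The cost is precision for every contrast. It matters most for light against sleep stabilization, the comparison that isolates the light itself, since stabilization is described as a component of the light treatment.

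**Working it through.** **Inputs from the article.** Standardized changes 0.47, 0.16 and 0.05; 103 per arm; two-sided alpha 0.05; one-way ANOVA. I take the effects as units of the SD of change, because the ANOVA is on change.

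**Assumptions.** The article gives no correlation (rho) between visit 3 and visit 7 FIQR, so I show a range. Variances at the two visits are taken as equal (s²).

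**1. The plan's own figure.** The mean of the three effects is 0.2267. The squared deviations sum to 0.2433² + 0.0667² + 0.1767² = 0.0949, so f = √(0.0949/3) = 0.178. The noncentrality is 103 × 0.0949 = 9.77 on 2 and 306 degrees of freedom. Power is 80.2%, and 103 is the smallest number per arm that reaches 80%. The stated power reproduces.

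**2. The missingness trigger.** 309/390 = 0.792, so about 21% are expected without complete data. That is above 15%, so the rule is expected to apply.

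**3. Reading A: visit 3 is a response.** The group indicators leave baseline means free in each arm. In 60 simulated complete data sets (rho 0.5, three visits, 103 per arm), the visit 7 time-by-group estimate equalled the raw difference in mean change to within 1e-14.

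- Variance of change: 2s²(1 − rho).
- Variance after adjusting for baseline: s²(1 − rho²).
- Ratio: (1 + rho)/2, a reduction of (1 − rho)/2.

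The simulation gave mean standard errors of 0.1197 (adjusted) and 0.1389 (mixed model as listed). The variance ratio is (0.1197/0.1389)² = 0.74, against 0.75 in theory. Dividing the noncentrality 9.77 by the ratio gives:

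| Assumed rho | Variance reduction | Omnibus power, baseline-adjusted | Per arm for 80% |
|---|---|---|---|
| 0.3 | 35% | 94% | 68 |
| 0.5 | 25% | 91% | 78 |
| 0.7 | 15% | 87% | 88 |
| 0.9 | 5% | 82% | 98 |

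The comparison is 80% power and 103 per arm for unadjusted change.

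For light against stabilization the difference is 0.47 − 0.16 = 0.31, with standard error √(2/103) = 0.139 and ratio 2.22. Power is about 60% unadjusted, 73% at rho 0.5 and 67% at rho 0.7.

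**4. Reading B: only later visits are responses.** The analysis is then of raw follow-up scores. Their variance relative to change is 1/[2(1 − rho)]: 0.71, 1.00, 1.67 and 2.50 at rho 0.3, 0.5, 0.7 and 0.8. Omnibus power is 92%, 80%, 57% and 40%. At rho 0.3 this beats raw change but is still below the 94% from adjustment.

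**5. Adding covariates to the model as listed.** Under Reading A with complete data, a participant-level covariate entered as a main effect cancels from the within-participant contrast. In the simulation the estimate agreed to 1e-14 and the mean standard error stayed at 0.1389. The structure of the model has to change, not only its covariate list.

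**The case against.** The strongest reply is that this is a condensed article, that a list introduced as what predictors will include need not be complete, and that an unseen analysis plan may add baseline terms. That would settle the matter if the article were silent. It is not: it names the fixed effects and gives a specific rule for when covariates enter, and under that rule baseline FIQR and the minimization factors are not planned adjusters. If the analysis plan does adjust, the article should be aligned with it.

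Second, nothing stated is invalid. This stands. The 80% power is calculated for unadjusted change and reproduces, and under Reading A the analysis matches it. A reader might infer that the trial is underpowered or the estimate biased. The documents support neither. The 60% for light against stabilization is not a broken promise either, because the article claims power only for the omnibus test.

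Third, the wording does not settle which reading applies. This stands too. Visit 3 falls after randomization but before treatment, so post-randomization time can be read either way. One cannot say flatly that the model analyses raw change.

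Fourth, a reader might infer that leaving out all four minimization factors has a measurable cost in precision, or that none of them can enter. Neither follows. No prognostic strength is given for age, sex or SDOH risk, so every gain above comes from baseline FIQR alone. The missingness rule could also admit any of them. Finally, the FIQR used in minimization must be the screening score, because allocation precedes visit 3. It is a different variable from the visit 3 baseline.

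**Conclusion.** The point holds as avoidable inefficiency. As stated, the model plans no adjustment for continuous visit 3 FIQR or for the minimization factors. Its only covariate rule, likely to be triggered, selects on missingness.

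Under Reading A, baseline adjustment removes (1 − rho)/2 of the variance, equivalent to 33%, 18% or 5% more patients at rho 0.5, 0.7 or 0.9 (1/0.75, 1/0.85, 1/0.95). Under Reading B the loss is larger than under Reading A once rho exceeds 0.5. The gain from adjustment is positive under Reading A for any rho below 1, and under Reading B for any rho other than 0.

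These sizes rest on an assumed rho, equal variances, complete data and effects in SD-of-change units. If rho is near 0.9 and visit 3 is a response, the benefit is small. Including age, sex and SDOH risk serves to match the analysis to the allocation. Standard errors tend to be conservative when prognostic minimization factors are left out, but the size of that effect cannot be given from the documents.

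**What to change.** 1. State whether visit 3 FIQR is a response in the primary model.
2. Model visit 7 and visit 8 FIQR with visit, group, group-by-visit, continuous visit 3 FIQR and baseline-by-visit. Alternatively, keep visit 3 as a response with baseline means constrained equal across arms.
3. Prespecify age group, sex and SDOH risk group as covariates in that model whatever the missingness. Any covariates that predict missingness would be additional.
4. Do the same for each BPI score, with its own visit 3 value.

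The cost is wording only. Every variable is already collected at screening, visit 1 or visit 3, and sample size and conduct are unaffected. With 55 enrolled by mid-July 2025 and final analysis due by June 2029, the change can be fixed well before outcome data are analysed.

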### Statistical Power and Analysis

We plan to enroll 390 individuals, aged 18 years or older, who meet the 2016 revised diagnostic criteria for fibromyalgia [45] and have at least mild fibromyalgia symptoms (FIQR score of ≥31) [48] (see Textbox 1). We aim for 309 participants with complete data (103 per each of the 3 groups), assuming 20% attrition during the 5-week study period. The sample size will provide 80% power to detect a difference in the standardized effect sizes (changes from baseline to post-treatment) of 0.47, 0.16, and 0.05 in FIQR in morning bright light treatment, sleep timing stabilization, and TAU groups, respectively, with a two-tailed 0.05 level 1-way ANOVA test. The effect size in the morning bright light treatment group is clinically meaningful and detectable based on our previous study [37]. The effect size in the sleep timing stabilization arm is 1/3 of that in the morning bright light group, and we conservatively estimated an effect size of 0.05 in the TAU group due to study participation. The study should also have adequate power to detect a binary outcome of clinically meaningful improvement (≥30% from baseline) or achieving a treatment response (≥16.8 decrease in FIQR) [83].

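### The 15% missing-data rule leaves the primary model's covariates unfixed, and covariates entered without a time interaction only partly protect the time-by-group estimate when they predict change and dropout differs by arm

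*Protocol article*

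**What the plan says.** All of this is in the protocol article, Statistical Power and Analysis, unless noted.

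- The primary and secondary outcomes are analysed by intention to treat with a "mixed-effects longitudinal data model with participants as random intercepts to account for between-participant variability".
- The treatment effect is carried by the time-by-group terms, because the fixed part of that model is given as follows: "Predictors will include post-randomization time, two intervention group indicators with TAU as the referent group, and the interactions of time by group indicators".
- The missing-data rule has a gate and a selection step: "if missingness is greater than 15%, we will use logistic regression to assess baseline characteristics predictive of missingness postrandomization". It then has an action: the analysts "will include those baseline characteristics as covariates in the final model". No interaction of these covariates with time or group is stated.
- The expected loss is above the gate: "We aim for 309 participants with complete data (103 per each of the 3 groups), assuming 20% attrition during the 5-week study period", from 390 enrolled.
- Randomization and Blinding names four minimization factors: FIQR band, age, sex and SDOH risk index.
- The Introduction hypothesizes that SDOH risk will affect both engagement with treatment and response to it.

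**The concern.** Two features of the stated rule deserve attention.

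First, the gate sits below the attrition that the plan itself expects. The rule is worded as a contingency but will in practice define the primary model. Which covariates that model contains will be known only once the missingness has been seen.

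Second, the action is aimed mainly at level, while the estimand is a difference in change. With complete data at two visits, a covariate that is constant over time cancels from each participant's change and leaves the time-by-group estimate untouched. With dropout it acts only indirectly, through the model's implicit prediction of the missing visit 7 score from the observed visit 3 score. If the characteristic predicts how much FIQR changes, and dropout depends on it differently by arm, that indirect route is too weak.

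The stake is a primary estimate that keeps part of its dropout bias while the report says that missingness was adjusted for.

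**Working it through.** **1. The plan's own figure.** Standardized changes 0.47, 0.16 and 0.05 have mean 0.227. Cohen's f = √[(0.243² + 0.067² + 0.177²)/3] = 0.178. With 103 per arm and alpha 0.05, the noncentral F gives power 0.802, and 103 is the smallest n per arm that reaches 80%. Also 309/0.8 = 386.25, so 387 are needed against 390 planned. The sample size reproduces and this point does not affect it.

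**2. Will the gate open?** More than 15% of 390 means at least 59 missing (0.15 × 390 = 58.5). With X ~ Binomial(390, p), P(X ≥ 59) is:

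| True missing rate p | P(gate opens) |
|---|---|
| 0.12 | 0.04 |
| 0.15 | 0.49 |
| 0.18 | 0.94 |
| 0.20 (planned) | 0.995 |

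**3. Does a plain covariate repair the estimate?** The stated random-intercept model was simulated with 390 participants, visits 3 and 7, and a true light-versus-TAU effect of −0.42 SD (0.47 − 0.05). These settings are assumptions, not document figures:
- Between- and within-person variances are 0.5 each (correlation 0.5).
- One binary baseline characteristic x has prevalence 50%.
- In (a) and (b), dropout in the light arm is 35% if x = 1 and 5% if x = 0, and 20% in the other arms.
- x effects are 0.5 SD in (a) to (c), 0.8 SD on level in (d), and 0.4 SD in (f). In (e), x adds 0.5 SD to level or to change.

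The entries are bias in the light-versus-TAU time-by-group estimate. Monte Carlo SE is about 0.0035 in (a) to (d), with 1,500 runs, and about 0.0055 in (e) and (f), with 600 runs.

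| Case | x omitted | x as main effect | x and x-by-time |
|---|---|---|---|
| (a) x predicts change; dropout differs by arm; 20% missing | −0.054 | −0.043 | −0.006 |
| (b) x predicts level and change; dropout as in (a) | −0.070 | −0.038 | −0.003 |
| (c) as (b), but 14% missing (gate closed) | −0.041 | not applied | +0.002 |
| (d) x predicts level only; dropout differs by arm | −0.045 | +0.002 | +0.002 |
| (e) dropout depends on x equally in all arms; no effect modification | about 0 | about 0 | about 0 |
| (f) x modifies the light effect; equal dropout by arm | −0.035 | −0.035 | −0.035 |

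In (f), adding x-by-group-by-time reduces the bias to −0.011.

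Share of bias left by the main effect: (a) 0.043/0.054 = 80%; (b) 0.038/0.070 = 54%. A second, separate simulation gave −0.042 falling to −0.034 (81% left) and −0.057 falling to −0.031 (54% left), with 0.005 or less once a time interaction was added.

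**4. Hand check.** Let x shift level by λ and change by δ, with within-person correlation ρ = 0.5. The correct prediction of a missing visit 7 score needs an x coefficient of λ(1 − ρ) + δ. A single main effect γ supplies γ(1 − ρ), and with complete data γ = λ + δ/2.
- (a) λ = 0, δ = 0.5: needed 0.5, supplied 0.25 × 0.5 = 0.125, so 75% is left.
- (b) λ = δ = 0.5: needed 0.75, supplied 0.75 × 0.5 = 0.375, so 50% is left.
- (d) δ = 0: needed and supplied are both λ/2, so nothing is left.

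These agree with the simulated 80%, 54% and full repair. Participants seen only at visit 3 pull γ a little towards λ, which explains the slightly larger simulated shares.

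**5. Size.** 0.043/0.42 = 10% and 0.038/0.42 = 9% of the assumed contrast. The sampling SD of the estimate is about 0.0035 × √1500 = 0.136 to 0.0037 × √1500 = 0.143, say 0.14. Residual biases of 0.031 to 0.043 are then about 0.2 to 0.3 standard errors.

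**The case against.** Five arguments count on the other side.

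- **The rule is not the only protection.** A reader might infer that nothing guards the estimate below 15%. The documents do not support that. The mixed model uses every observed score and is valid when missingness depends only on observed outcomes and model terms. With visit 3 FIQR as a response, dropout driven by baseline severity is already handled. This stands. What is absent below the gate is protection against other baseline predictors of both dropout and change.
- **The covariates can work.** A reader might infer that the planned adjustment never repairs the effect estimate. Case (d) refutes that, and case (e) shows that there may be nothing to repair. This stands, so the point is conditional.
- **The choice is not free.** A reader might infer that analysts could pick covariates to suit the result. Selection uses missingness and baseline data, not outcome values or treatment effects, and the rule is written in advance. This stands. The remaining complaint is only that the covariate set is not known beforehand.
- **Detail may lie elsewhere.** Entering variables as covariates does not exclude time interactions, and a candidate list or sensitivity analyses may be in a full analysis plan that is not shown. This is fair, and no criticism is made of those omissions. The gate, the selection step and the manner of entry are nevertheless stated, and a main effect is the ordinary reading.
- **Arm-specific dropout is assumed.** No figure in the article supports the rates used. This stands. It is plausible, because the light arm carries a daily one-hour task for 28 days while TAU keeps its usual sleep, but it is not documented.

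**Conclusion.** The point holds in a conditional form. Under the trial's own attrition assumption the gate opens with probability about 0.99, so the primary model's covariates will not be fixed in advance. Entered without a time interaction, a characteristic that predicts change leaves roughly half to four fifths of the bias when dropout depends on it differently by arm. That is about 0.03 to 0.04 SD, up to 10% of the assumed 0.42 contrast, or 0.2 to 0.3 standard errors. In the simulated direction it flatters the light arm; the opposite sign is equally possible.

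The same mechanism at 14% missing gives a bias of 0.041 SD with the rule inactive, so 15% is not a threshold below which bias is absent. Where the characteristic modifies the treatment effect, even a time interaction is not enough. This matters because the article itself expects SDOH risk to influence response.

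This rests on the assumed simulation settings, on reading the rule as main effects, on applying the 15% to FIQR at visit 7, and on visit 3 FIQR being the first response in the model. It is a modest but nearly free improvement to a stated rule. It is not an internal contradiction, and it leaves the sample size unchanged.

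**What to change.** - Remove the 15% gate and the logistic selection step from the primary analysis. The logistic regression can stay as a description of who dropped out.
- Name the covariates now: the minimization factors age, sex and SDOH risk index, plus baseline PHQ-9 and baseline PROMIS Sleep Disturbance. All are already collected. Give each a visit interaction and use them whatever the missingness.
- Decide the role of visit 3 FIQR. Either keep it as an outcome in the model, or use it as a covariate with post-baseline scores as the only outcomes, but not both.
- Because response is hypothesized to depend on SDOH risk, add the SDOH-by-group-by-time term, or impute by arm, in a supporting analysis.

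The cost is a change of wording and a few parameters. Five covariates with a main effect and one visit interaction each add 5 × 2 = 10 terms for visits 3 and 7 (15 if visit 8 is modelled as a further level), against 309 expected completers. The article reports 55 enrolled by mid-July 2025 and data collection until March 2029, so the change can be made well before the final data exist.
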